## Abstract

**Introduction:**

Postmenopausal bleeding (PMB), the red flag symptom for endometrial cancer, triggers urgent investigation by transvaginal ultrasound scan, hysteroscopy and/or endometrial biopsy. These investigations are costly, invasive and often painful or distressing for women. In a pilot study, we found that voided urine and non-invasive vaginal samples from women with endometrial cancer contain malignant cells that can be identified by cytology. The aim of the DEveloping Tests for Endometrial Cancer deTection (DETECT) Study is to determine the diagnostic test accuracy of urine and vaginal cytology for endometrial cancer detection in women with PMB.

**Methods and analysis:**

This is a multicentre diagnostic accuracy study of women referred to secondary care with PMB. Eligible women will be asked to provide a self-collected voided urine sample and a vaginal sample collected with a Delphi screener before routine clinical procedures. Pairs of specialist cytologists, blinded to participant cancer status, will assess and classify samples independently, with differences settled by consensus review or involving a third cytologist. Results will be compared with clinical outcomes from standard diagnostic tests. A sample size of 2000 women will have 80% power to establish a sensitivity of vaginal samples for endometrial cancer detection by cytology of ≥85%±7%, assuming 5% endometrial cancer prevalence. The primary objective is to determine the diagnostic accuracy of urogenital samples for endometrial cancer detection by cytology. Secondary objectives include the acceptability of urine and vaginal sampling to women.

**Ethics and dissemination:**

This study has been approved by the North West–Greater Manchester West Research Ethics Committee (16/NW/0660) and the Health Research Authority. Results will be disseminated through publication in peer-reviewed scientific journals, presentation at conferences and via charity websites.

**Trial registration number:**

ISRCTN58863784.

Strengths and limitations of this studyThis is a prospective evaluation of a novel, non-invasive endometrial cancer detection tool that could transform diagnostic pathways for women with postmenopausal bleeding (PMB).Samples will be taken prior to routine clinical procedures to avoid inadvertent contamination of samples by iatrogenically dislodged endometrial cells.Cytologists are blinded to participant cancer status until they provide their consensus report.Passive follow-up of participants will ensure missed cancer diagnoses are minimised.Recruitment is limited to women with PMB, and results may not be applicable to premenopausal women or those with atypical presentations of endometrial cancer.

## Introduction

In the UK, over 9000 women are diagnosed with endometrial cancer every year.^1^ The red flag symptom for endometrial cancer is postmenopausal bleeding (PMB).^2^ A woman with PMB is referred by her general practitioner (GP) on the urgent ‘suspected cancer’ pathway to a rapid access gynaecology clinic, where she is offered a series of invasive, unpleasant and often painful tests to rule out endometrial cancer.^3^ These include transvaginal sonography (TVS), outpatient hysteroscopy and endometrial biopsy.^4^ Together, these tests cost the National Health Service (NHS) around £750/woman.^5^ PMB is extremely common, and only 5%–10% of women with PMB are ultimately diagnosed with endometrial cancer.^6 7^ Indeed, it has been estimated that 5% of all GP referrals to gynaecology, as many as 150 000 women per year in the UK alone, relate to PMB.^5^ A simple, non-invasive test deployed in primary care to target those at risk of endometrial cancer for invasive testing, while safely reassuring the vast majority of healthy women, could transform diagnostic pathways for endometrial cancer. In the UK, it would save thousands of women every year from the psychological and physical sequelae of invasive tests and create substantial cost savings for the NHS (potential saving in excess of £100 million/year).

The development of novel non-invasive detection tools was voted the most important research priority for detecting cancer early in the recently completed James Lind Alliance Priority Setting Partnership.^8^ In endometrial cancer, the anatomical continuity between the uterus and the lower genital tract facilitates the collection of shed tumour cells using non-invasive sampling methodologies.^9–13^ We found that shed tumour cells can be collected from the vagina by gentle lavage using the Delphi screener and from voided urine samples, which are inevitably contaminated by endometrial debris in women with uterine bleeding.^14^ These cells can be distinguished from normal squamous, urothelial and glandular cells of the urogenital tract by cytology, although certain benign mimics (eg, polyps and atrophy) can cause difficulties with interpretation. In our pilot study of 113 women with unexplained PMB, urine and/or vaginal cytology showed 100% sensitivity and 100% negative predictive value (NPV) for endometrial cancer detection; it identified all seven cancers (four endometrial, one cervical, one ovarian and one bladder) for a 11% false positive rate. Furthermore, mean pain scores were significantly lower for vaginal sampling (1.61, SD 2.04) than for diagnostic hysteroscopy (4.28, SD 2.61, p<0.001) and endometrial biopsy (4.88, SD 3.49, p<0.001), respectively.^14^ Thus, urogenital cytology has considerable potential as a well-tolerated ‘rule out’ test to enable quick reassurance for most women who present to primary care with PMB and urgent referral for those who test positive. To confirm its clinical utility for endometrial cancer detection, urine and vaginal cytology must now be tested in a large prospective study of women undergoing investigation for PMB. The aim of the DEveloping Tests for Endometrial Cancer deTection (DETECT) Study is to estimate the diagnostic accuracy of urine and vaginal samples for endometrial cancer detection by cytology in women with PMB.

## Methods

This protocol is reported in accordance with Standards for Reporting of Diagnostic Accuracy Studies (STARD) guidelines.^15^

### Study design

DETECT is a prospective multicentre diagnostic accuracy study of urine and vaginal cytology for endometrial cancer detection in women with PMB (study schema, figure 1).

**Figure 1 F1:**
[figure not shown]
Study schema illustrating the flow of participants through the study, interventions and evaluations. DETECT, DEveloping Tests for Endometrial Cancer deTection; PMB, postmenopausal bleeding.

### Participants and recruitment

Consecutive women will be recruited from gynaecology clinics at seven hospital sites across the North West England: St Mary’s Hospital, Trafford General Hospital, Wythenshawe Hospital, Royal Oldham Hospital, North Manchester General Hospital, Fairfield General Hospital and Tameside Hospital.

### Inclusion criteria

Women who have been referred to secondary care for investigation of PMB.Written, informed consent to participate.

### Exclusion criteria

Abnormal bleeding before the menopause.Previous treatment for endometrial cancer.Previous hysterectomy.Mirena coil in situ or removed within the last 3 months.Any other condition that would compromise participant safety or data integrity.

PMB will be defined as vaginal bleeding that occurs more than 12 months after menstruation has stopped due to menopause.

### Participant withdrawal

Participants may withdraw from the study at their own request or at the discretion of the investigator. Withdrawal from the study will not affect patient care.

### Sample size

With a sample size of ~2000 women and an endometrial cancer prevalence of 5%,^5^ there will be approximately 1900 women without endometrial cancer and 100 women with endometrial cancer. The study will have 80% power to determine the sensitivity of the test at ≥85%±7% and the specificity of the test at ≥85%±2%. At 85% specificity, around 1630 women will have a negative test result, giving the test a NPV) of 99.1% (98.5% and 99.4%). These estimates originate from the pilot study, where sensitivity and specificity were both >85%. The prevalence of endometrial cancer will determine the final sample size. If the prevalence of endometrial cancer is greater than 5%, fewer than 2000 women will be needed; if it is less than 5%, more women will be needed to determine the sensitivity of the test at ≥85%±7%.

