Analysis of the primary objective will compare the clinical performance of cytology with the reference test. Thus, sensitivity, specificity, NPV, positive predictive value and diagnostic accuracy will be reported together with their corresponding 95% CIs, calculated using the exact binomial method. Where a histology result is not available, endometrial thickness <4 mm (histology not indicated) or discharge from diagnostic workup will be used as reference standard. Analysis of the secondary objectives will assess clinical performance of the urine test alone and the vaginal test alone for the detection of endometrial cancer in relation to the reference test. The clinical performance of urine and vaginal cytology for the detection of any cancer affecting the pelvic organs will also be calculated. Secondary analyses will follow the same approach as the primary analysis. Sensitivity analyses will consider the clinical performance of cytology with a broader definition of a positive cytology result (including glandular results as test positives). Interobserver agreement between the cytopathologists will be assessed using the kappa statistic and categorised as poor, fair, moderate and good. McNemar’s χ^2^ test will be used to compare urogenital cytology with routine diagnostics. Multivariate logistic regression will evaluate the relationship between positive cytology and endometrial cancer diagnosis while adjusting for potentially predictive clinical characteristics like age and BMI. The diagnostic accuracy of urogenital cytology will be compared with individual elements of the standard diagnostic pathway, including TVS, hysteroscopy and endometrial biopsy. Consideration will be given as to where in the current diagnostic pathway for endometrial cancer urogenital cytology fits. Its use as a triage test prior to any other diagnostic workup both alone and in combination with clinical parameters (eg, age and BMI) will be modelled. We will also consider its usefulness in combination with transvaginal ultrasound scanning at various endometrial thickness cut-offs. The acceptability of urogenital sampling will be compared with transvaginal ultrasound, hysteroscopy and endometrial biopsy (online supplemental appendix 1).

10.1136/bmjopen-2021-050755.supp1Supplementary data

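### The 80% power stated for sensitivity does not follow from the sample-size inputs: with about 100 cancers, ±7% is a 95% confidence half-width

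*Protocol article*

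**What the plan says.** The Sample size section of the protocol article starts from about 2000 women and 5% prevalence, so that "there will be approximately 1900 women without endometrial cancer and 100 women with endometrial cancer". It then states: "The study will have 80% power to determine the sensitivity of the test at ≥85%±7% and the specificity of the test at ≥85%±2" (per cent). The Abstract (Methods and analysis) makes the claim for sensitivity only and ties it to one specimen: the study "will have 80% power to establish a sensitivity of vaginal samples for endometrial cancer detection by cytology of ≥85%±7" (per cent). The only support given for the assumed values is "These estimates originate from the pilot study, where sensitivity and specificity were both >85" (per cent).

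The final number of women is to be adjusted so that the sensitivity target is kept. Under Statistical analyses, the primary analysis is estimation: sensitivity and specificity with 95% confidence intervals "calculated using the exact binomial method". That section plans no test of either quantity against a threshold.

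**The concern.** Power is the probability that a named test rejects a named null value when a named alternative is true. A ± margin is the expected width of a confidence interval. The sentence joins the two and supplies none of the elements that would define a power.

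This matters most for sensitivity, because that target sets the sample size, is the only power statement in the Abstract, and is the critical property of a test proposed for ruling cancer out. A reader of the Abstract will conclude that the study has a four-in-five chance of demonstrating sensitivity at or near 85%. If the 80% does not come from the stated inputs, that reader is misinformed about how firmly the study can exclude a clinically poorer sensitivity.

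**Working it through.** **Inputs from the Sample size section:** 100 women with cancer, 1900 without, expected value 85% for both measures, margins of 7 and 2 points, power 80%. **From Statistical analyses:** exact binomial 95% intervals. **Assumed here, because the document gives none for the power claim:** alpha 0.05, tried one-sided and two-sided.

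**1. Reproducing the margins.** Wald 95% half-width = 1.96 × √(p(1−p)/n).
- Sensitivity: 1.96 × √(0.85 × 0.15/100) = 0.0700, or 7.0 points. The stated ±7% is reproduced, and no power term enters.
- Specificity: 1.96 × √(0.85 × 0.15/1900) = 0.0161, or 1.6 points. This equals the stated ±2% only after rounding to a whole point.

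**2. Sensitivity read as a test, n = 100.** For each null p0, take the smallest count r with P(X ≥ r | 100, p0) ≤ 0.025 (two-sided) or ≤ 0.05 (one-sided). Power is P(X ≥ r | 100, p1).

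| Null against alternative | Sidedness | r | Exact power | Null-variance normal formula |
|---|---|---|---|---|
| 78% against 85% | two-sided | 87 | 35% | 38% |
| 78% against 85% | one-sided | 86 | 46% | 52% |
| 85% against 92% | two-sided | 93 | 45% | 50% |
| 85% against 92% | one-sided | 92 | 59% | 66% |

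None is near 80%. By the null-variance formula, 80% power would need 253 cancers (two-sided) or 197 (one-sided) for 78% against 85%, and 176 or 136 for 85% against 92%.

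**3. Sensitivity read as assurance of width.** If true sensitivity is 85%, the probability that the 95% half-width is at most 7 points is 57% for the Wald interval and 25% for the exact interval.

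**4. Dependence on the true value.** Exact two-sided power to exclude 78% with 100 cancers (r = 87):

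| True sensitivity | 85% | 88% | 89% | 90% |
|---|---|---|---|---|
| Power | 35% | 69% | 79% | 88% |

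**5. Specificity, n = 1900, same method.**
- 85% against 87%: one-sided 80.4% (r = 1641); two-sided 70% (r = 1646).
- 83% against 85%: one-sided 75% (r = 1605); two-sided 64% (r = 1610).

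The first one-sided reading does return the stated 80%.

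**6. What the planned interval delivers.**
- 85/100: exact 95% CI 76.5% to 91.4%, that is −8.5 and +6.4 points.
- 1615/1900: exact 95% CI 83.3% to 86.6%.

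**The case against.** Several points on the other side have weight.

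*Some readings do give about 80%.* For specificity, the one-sided 5% test of 85% against 87% gives 80.4%. For sensitivity, a one-sided formula for 85% against 92% that uses only the variance under the alternative gives 82.5% (93 cancers for 80%). It would therefore be wrong to infer that every power reading fails. But the document states neither test, and the exact test of that same sensitivity contrast gives 59%.

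*The target is at least 85%, not exactly 85%.* This stands: the 35% is the low end of the stated range, and power rises with the true value. The Introduction reports 100% pilot sensitivity. That rested on seven cancers of all sites, four of them endometrial; the exact lower 95% limit is 0.025^(1/7) = 59% for 7/7 and 0.025^(1/4) = 40% for 4/4. It does not establish a value near 89%, and the Sample size section does not assume one.

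*Asymmetry is normal for exact intervals.* This also stands. The average half-width for 85/100 is (91.4 − 76.5)/2, about 7.4 points. The lower arm of 8.5 points is still worth stating for a rule-out test.

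Two stronger inferences should be resisted. First, a reader might note that if true sensitivity is exactly 85%, the lower limit reaches 85% only about 1% of the time. That is the type I error at the null, capped at 2.5% for any sample size, and says nothing about this design. Second, from "If the prevalence of endometrial cancer is greater than 5%, fewer than 2000 women will be needed" a reader might infer that ±2% for specificity and the stated negative predictive value fail whenever prevalence exceeds 5%. With 100 cancers fixed, the specificity half-width is 1.8 points at 6% prevalence (1567 women without cancer), 1.9 at 7% (1329), 2.1 at 8% (1150) and 2.3 at 10% (900), so ±2% holds at 6% and 7%. At 10% prevalence the predictive value falls to 1530/1560 = 98.1% with all 2000 women and to 765/780 = 98.1% with 1000. Prevalence causes the fall; stopping earlier only widens the interval.

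**Conclusion.** The 80% power stated for sensitivity in the Abstract and the Sample size section does not follow from the stated inputs. The ±7% is a Wald 95% half-width. At an assumed alpha of 0.05 and a true sensitivity of 85%, exact power to exclude 78% is 35% two-sided or 46% one-sided. For 85% against a true 92% it is 45% or 59%. The two-sided figure against 78% comes close to 80% only at a true sensitivity of about 89%, which the document does not state.

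For specificity the criticism is narrower: 80% is attainable, but only under a one-sided test that the document does not name.

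The result rests on the assumed alpha, on the contrasts implied by 85% ± the margin, and on 100 cancers being observed. It is an error in a stated figure. The planned analysis, which is estimation with exact intervals, is unaffected.

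**What to change.** Delete the 80% power claim in the Abstract and in the Sample size section and state precision with the interval method that will be used. Suggested text: *With about 100 cancers, an observed sensitivity of 85% has an exact 95% CI of 76.5% to 91.4%; with about 1900 women without cancer, an observed specificity of 85% has an exact 95% CI of 83.3% to 86.6%.*

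If a power statement is kept, name the null, the assumed true value, alpha and the sidedness. For 100 cancers, true sensitivity 85% and an exact two-sided 5% test, power is 84% against a null of 72% (r = 82), 67% against 75% (r = 84) and 35% against 78% (r = 87). For specificity, name the one-sided 85% against 87% test if that is where the 80% came from.

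The cost is wording only. Patient numbers and analyses stay as they are; the downside is that the published figure becomes less favourable.

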### Study duration

In the pilot study, 90% of eligible women agreed to participate. Women will be recruited between September 2018 and September 2021 with clinical outcome data collected until March 2022. To achieve the recruitment target of ~2000 women, approximately 20 women will be recruited per week across the seven hospital sites. A temporary pause on recruitment to the study was initiated in March 2020 because of the COVID-19 pandemic. Recruitment recommenced in June 2020 but with COVID-19 restrictions in place, meaning that recruitment rate is slower than pre-pandemic (approximately 10 women per week across recruitment sites).

### Invitational procedure

Eligible women will be identified from referral letters and clinic lists by hospital clinical staff. A letter inviting participation and a detailed participant information sheet (PIS) will be sent by post to their home address. Potential participants will have the opportunity to discuss the study over the telephone with members of the study research team prior to their appointment. Due to the urgent nature of referrals, some women are offered short-notice clinical appointments by telephone. Where there is insufficient time for invitational material to be received by post, women will be informed about the study via telephone and/or invited to participate on arrival at the clinic. Women will be invited to read the PIS and ask questions about the study before providing written, informed consent to participate.

### Baseline clinical data

The following demographical and baseline clinical data will be obtained: age, ethnicity, socioeconomic status, education level, body mass index (BMI), smoking status, parity, age of menopause, use of contraceptives, hormone replacement therapy or tamoxifen, history of hypertension, hypercholesterolaemia, diabetes mellitus, polycystic ovary syndrome, thyroid disease, coagulopathy, Lynch syndrome, cervical screening history, endometrial hyperplasia and personal or family history of cancer. Women will be asked in detail about their help-seeking behaviour and the onset, duration and extent of their PMB.

### Index tests

The timing of urine and vaginal sampling is important to ensure validity of the results. Both research samples will be taken before any routine clinical procedures to avoid inadvertent contamination with iatrogenically dislodged endometrial cells (study schema, figure 1). Of the two research samples, urine will be collected first because vaginal sampling will remove naturally shed uterine debris from the lower genital tract and affect interpretation of the results.

### Urine samples

Using both written and verbal instructions, we will ask women to bring to clinic a first catch sample of their first urinary void of the day, collected in a sterile pot. A second voided urine sample will be collected by the participant on arrival at the clinic, before any other research or clinical procedures are carried out. This will ensure that every woman has at least one satisfactory urine sample available for analysis.

### Vaginal sample

The vaginal sample will be taken by the research practitioner using a Delphi screener (Rovers Medical Devices, Oss, the Netherlands)^16^ according to the following protocol, with the participant in the supine position, knees bent and legs apart. The Delphi screener is inserted into the posterior fornix of the vagina and 3 mL saline expelled from its reservoir by depressing the plunger for 3 s. The sample is then collected by suction following release of the plunger while slowly rotating and withdrawing the device. A dry pot at the introitus collects any residual fluid. Additional samples are obtained by refilling the reservoir with saline and repeating the steps above until clear fluid is obtained (maximum of three times).

### Sample handling

Urine samples will be tested for haematuria by dipstick. Urine and vaginal samples will be fixed with equal volumes of BD CytoRich Red Preservative (Becton, Dickinson and Company, the USA) to preserve cellular integrity, prevent degradation and inhibit bacterial overgrowth. Samples will be sent to the Manchester Cytology Centre at the Manchester University NHS Foundation Trust (MFT). Samples will be anonymised and labelled with sample type (urine or vaginal fluid) and a unique study identifier (study ID) to prevent accidental unblinding of the cytopathology team. With the exception of whether the participant is taking exogenous hormones, all clinical data will be withheld from the cytology team until consensus results are received. Second urine samples will be fixed with BD CytoRich Red Preservative and stored at 4°C until the first urine sample has undergone cytological assessment. This second sample will undergo cytological review if the first urine sample is inadequate for analysis or post hoc, if the first urine sample is false negative for endometrial cancer detection. Residual samples will be stored in the MFT Biobank for future biomarker discovery work. Samples will be either embedded in agar cell blocks to preserve cellular integrity for future immunocytochemistry or centrifuged to pellet the cellular material. The resulting pellet plus aliquots of the supernatant will be stored at −80°C.

